#### Secondary

Determination of side effects from levetiracetam in the study population compared to placebo. Anti-seizure medications are generally well-tolerated in people with epilepsy, but are not routinely administered to people who have not had a seizure. It is therefore clinically essential to determine if there are side effects in this patient group. This will be enquired about at each study contact.Determination of the effect on mood of levetiracetam in the study population compared to placebo using standardised scales such as Neuropsychiatry Index. Given that levetiracetam can have an adverse effect on mood, this will be specifically evaluated and monitored throughout. Principal comparisons will be between the start and end of each arm of the study.Determination of the effect on quality of life from levetiracetam in the study population compared to placebo using standardised scales such as the BADLS, EQ-5D and DSRS index (compare end of arm 1 to baseline and end of arm 2 to end of arm 1). Even were levetiracetam to not show an advantage on cognitive measures, were it to improve quality of life in people with AD that may make it a worthwhile treatment.Assessment and modelling of the EEG prior to starting levetiracetam and correlation with response to levetiracetam. It may well be that levetiracetam is not suitable for all people with AD. EEG could offer a simple non-invasive biomarker to better determine who may benefit from levetiracetam and similarly who may experience side effects. The EEG is performed at baseline and will be modelled and correlated with outcomes for each participant at study end.

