Screening visit: patient screened against inclusion/exclusion criteriaBaseline and randomisation visit: eligible patients who consent to participation are evaluated as outlined and randomised to either receive levetiracetam first or placebo first. Baseline data are captured as detailed in baseline assessmentsTelephone call 2 weeks after randomisation: as levetiracetam/placebo is uptitrating, there will be a telephone call at 2 weeks to ensure no adverse effects and document adherence4-week visit when participants in the active arm will have reached levetiracetam 500 mg twice daily.Eight week efficacy visit to evaluate effect of levetiracetam/placebo using all of the measures performed at the baseline visit.12-week crossover visit. Participants who were randomised to levetiracetam will have weaned to nil and start to take placebo and vice versa. Vital signs, adverse effects and adherence will be recorded. The cognitive and neuropsychiatric measures undertaken at baseline will be repeated to ensure no ‘carry over’ effect from patients who received levetiracetam initially.Telephone call 14 weeks after randomisation: as levetiracetam/placebo is uptitrating, there will be a telephone call at 2 weeks to ensure no adverse effects and document adherence16-week visit when participants in the active arm will have reached levetiracetam 500 mg twice daily.20-week efficacy visit (8 weeks after cross over visit) to evaluate effect of levetiracetam/placebo using all of the measures performed at the baseline visit.24-week end-of-study visit, 24 weeks post baseline. At this visit, patients will have weaned from either levetiracetam or placebo completely. Vital signs, medication adherence and adverse effects will be recorded.Telephone call at 28 weeks after randomisation, 4 weeks after weaning from study medication to document any adverse events from medication

Participants can also make unscheduled visits if required. These visits will be triggered by the participant at any stage through the trial should concerns, particularly relating to possible adverse effects, arise. If an unscheduled visit is required, dependent on the reason for the visit, the visit may occur at the clinical research site, at the participant’s home or telephonically.

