### Outcomes {12}

#### Primary

Changes in cognition in patients while taking levetiracetam as measured by computerised assessment of hippocampal binding memory task. Measures will be compared as change from baseline in each arm of the study (namely compare end of arm 1 to baseline and end of arm 2 to measures taken at start of arm 2). Were the study to show that levetiracetam can stabilise or even improve cognitive testing on a very specific task that evaluates hippocampal function that would open an entirely new therapeutic avenue for people with Alzheimer’s disease.

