## Statistical methods

### Statistical methods for primary and secondary outcomes {20a}

A trial-specific statistician based at the Centre for Statistics in Medicine, University of Oxford, will perform statistical analysis.

As the trial is crossover in design, all analyses will be within participants, comparing outcome measures after taking the placebo and after taking levetiracetam. Thus, the analyses of the primary and secondary outcomes relating to cognition, behaviour and quality of life will be based on the differences between the observations at the efficacy visits (week 8 and week 20) of the levetiracetam and placebo periods.

Within a given patient, levetiracetam and placebo will be compared using the paired t-test and the analysis of covariance adjusting for baseline values. We will compare results at 8 weeks to the initial baseline testing and at 20 weeks to the further baseline testing at 12 weeks. All results will be presented with 95% confidence intervals. For each carer who has consented to provide data, quality of life measures will likewise be compared between the observations at the week 8 and week 20 visits. Appropriate sensitivity analyses will be performed to confirm the robustness of the data.

EEG will be computationally analysed, after standard cleaning, downsampling and artefact rejection. Typical EEG data features of interest include time series measures (for example, mean, variance, skewness, kurtosis and coastline), frequency based features (e.g. band-passed power and rhythmicity) and channel pair-wise bivariate connectivity metrics. These baseline EEG features will be correlated with clinical outcome measures.

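### The Outcomes section refers arm-2 quality of life to the end of arm 1, which conflicts with the statistical section and, if applied as change scores from week 8, overstates a true effect by half on average

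*Protocol article*

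**What the plan says.** The Protocol article gives three accounts of the reference value for the second treatment period.

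- **Outcomes {12}, Secondary (quality of life: BADLS, EQ-5D, DSRS):** "compare end of arm 1 to baseline and end of arm 2 to end of arm 1".
- **Outcomes {12}, Primary (memory-binding task):** "compare end of arm 1 to baseline and end of arm 2 to measures taken at start of arm 2".
- **Statistical methods {20a}:** "analyses of the primary and secondary outcomes relating to cognition, behaviour and quality of life will be based on the differences between the observations". Those meant are the week-8 and week-20 efficacy assessments. The next paragraph adds: "We will compare results at 8 weeks to the initial baseline testing and at 20 weeks to the further baseline testing at 12 weeks".

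Subsequent visits says when measurements are taken. Week 8 is described as "Eight week efficacy visit to evaluate effect of levetiracetam/placebo using all of the measures performed at the baseline visit", and week 20 as "20-week efficacy visit (8 weeks after cross over visit) to evaluate effect of levetiracetam/placebo using all of the measures performed at the baseline visit". At the week-12 crossover visit, "The cognitive and neuropsychiatric measures undertaken at baseline will be repeated to ensure no" carry-over; quality of life is not named there. At week 24, "Vital signs, medication adherence and adverse effects will be recorded", again with no quality-of-life scale named. Participants are allocated 1:1 to the two sequences, 15 in each. Study drug is tapered to nil by week 12, and the authors judged a washout unnecessary.

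**The concern.** In a crossover trial, the reference for period 2 should not itself contain a treatment effect. If the end of arm 1 is the week-8 visit, the quality-of-life bracket uses an on-treatment value as the arm-2 reference. For someone who took levetiracetam first, any benefit at week 8 is counted once as a gain on levetiracetam and again as a loss on placebo.

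The Outcomes section says that a quality-of-life gain could make the drug worthwhile even without a cognitive advantage, and the abstract foresees rapid progress to a larger study. The size of a quality-of-life effect from this pilot would inform that planning. Two incompatible rules for the same outcome also leave room to choose between them after the data are seen.

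**Working it through.** **Is there a plan figure to reproduce?** The article gives no effect size or variance for quality of life. Its one design calculation concerns the memory task: mean difference 2.1%, SD of the difference 3%, so 2.1/3 = 0.7. A two-sided 5% paired t-test has power 0.894 with 23 patients and 0.907 with 24, so the stated 24 is reproduced. It plays no part below, where the true quality-of-life effect is left as t.

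**Inputs.** On-treatment values at weeks 8 and 20 (Subsequent visits); 1:1 sequences (Intervention description; Sequence generation); no carry-over (the authors' reason for omitting a washout). Write Y0, Y8, Y12 and Y20 for the visit values, and p1 and p2 for the period shifts at weeks 8 and 20 relative to baseline.

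**Bracket rule, end of arm 1 = week 8, change scores compared**

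| Sequence | Arm-1 change (Y8 − Y0) | Arm-2 change (Y20 − Y8) | Levetiracetam minus placebo |
|---|---|---|---|
| Levetiracetam first | t + p1 | p2 − p1 − t | 2t + 2p1 − p2 |
| Placebo first | p1 | t + p2 − p1 | t + p2 − 2p1 |

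With equal sequences the period terms cancel: (2t + t)/2 = 1.5t. With a share q of levetiracetam-first completers, the multiplier is 2q + (1 − q) = 1 + q. That is 1.42 for 10 of 24 and 1.58 for 14 of 24, and the period terms then leave a remainder (2q − 1)(2p1 − p2).

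**Direct rule in the statistical section (week 8 versus week 20)**

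Levetiracetam first: t + p1 − p2. Placebo first: t + p2 − p1. With equal sequences the mean is t.

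**Precision.** Assume independent visit errors with equal variance w². The bracket contrast is ±(2Y8 − Y0 − Y20), with variance (4 + 1 + 1)w² = 6w². The direct difference has variance 2w². The within-sequence SD ratio is √(6/2) = 1.73.

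**Simulation check** (400,000 patients, t = 1, assumed between-patient SD 1.5 and residual SD 1, no period effects): bracket rule 1.50 overall (2.00 and 1.00 by sequence); arm 2 referred to week 12, 0.998; direct difference 1.001. Adding assumed period effects left the bracket rule at 1.50.

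**Carry-over (assumed).** If 10% or 25% of the effect persisted at week 20, the bracket multiplier would be 1.45 or 1.375, and the direct difference 0.95 or 0.875.

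**ANCOVA with week 8 as the arm-2 baseline.** A within-participant form (difference in outcome on difference in baseline) gave about 0.74 to 0.83 of t under the assumed variances and period effects. A form pooling both periods gave about 1.1 to 1.45 for between-patient SDs of 0.5 to 3. So it too is biased, but the size and even the direction depend on the model.

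**Alternative reading: end of arm 1 = week 12 both times, with week 20 as the end of arm 2.** The arm-1 change is then Y12 − Y0, taken after the taper. Ignoring period effects, levetiracetam-first patients contribute 0 − 0 = 0 and placebo-first patients t − 0 = t, a mean of 0.5t. The bracket recovers t only if the same phrase means week 8 in its first half and week 12 in its second.

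**The case against.** The strongest reply is that the statistical section already contains the sound analysis. It names quality of life and bases the comparison on the week-8 versus week-20 difference for patients, with the same for carers. The bracket sits in an outcome description, and an analyst following the statistical section would never apply it. This stands. A reader might infer that the trial's quality-of-life results will be inflated by 50%. The documents do not support that: it happens only if the bracket is followed and raw change scores from week 8 are compared.

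The end of arm 1 is also nowhere defined, and dosing in arm 1 runs down to nil at week 12. Week 8 is therefore an inference. It is the better one, because the statistical section compares week 8 with baseline, the full set of measures is scheduled at weeks 8 and 20, and the primary outcome speaks of the start of arm 2 when that is meant. The week-12 reading does not rescue the bracket in any case, as shown above.

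Three further inferences would go too far:

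- **That no week-12 quality-of-life data exist.** The visit list is introduced as a brief summary, and the visit schedule (Fig. 2) is not shown. The text names only cognitive and neuropsychiatric measures at week 12, which leaves the matter open.
- **That the rule manufactures a benefit.** With balanced sequences and t = 0, the expected contrast is zero. The rule distorts the size of a real effect, in either direction of benefit or harm.
- **That the article already prescribes a period term.** It does not, for patients or carers.

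**Conclusion.** The conflict is real and stands on the text alone: the quality-of-life bracket cannot be reconciled with the statistical section, and it differs from the rule for the primary outcome. It is not a detail left to the analysis plan, because the article itself states both rules.

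The size is conditional. The 1.5t result requires week 8 as the end of arm 1, a comparison of raw change scores, 1:1 sequences among those analysed, and no carry-over. It averages a doubling in levetiracetam-first patients and no inflation in placebo-first patients, before period effects. The SD ratio of 1.73 also needs independent, equal-variance visit errors. Under ANCOVA the bias takes another size and possibly the opposite sign. Only BADLS, EQ-5D and DSRS are affected; the primary outcome is not. The point should be corrected because the rule as written gives a wrong estimate under either consistent reading, not because the trial's results are bound to be wrong.

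**What to change.** Delete the bracketed comparison from the quality-of-life item in Outcomes {12}. State instead that, for patients and carers, quality of life is analysed as the within-participant levetiracetam-minus-placebo difference between the week-8 and week-20 values, in line with Statistical methods {20a}.

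Check the visit schedule for week 12. If the quality-of-life scales are collected then, week 12 may serve as the arm-2 baseline; if not, say that the week-12 reference in {20a} does not apply to these outcomes. In no case should the week-8 value be used as a baseline, whether in change scores or as a covariate.

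A period term is an optional addition. It would protect the direct difference if the sequences end up unequal, where a remainder (2q − 1)(p1 − p2) would otherwise stay in the estimate.

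The cost is a line or two of protocol and analysis-plan text, with no new data and no change to visits or sample size.

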### Participant timeline {13}

The participant timeline and visit schedules are illustrated in Figs. 1 and 2.

### Sample size {14}

The trial is relatively short and one would not anticipate being able to detect changes in ADAS-Cog over this time-frame. Therefore, the trial is powered to detect a standardised effect of 0.7 in a specific and sensitive test of hippocampal function that has already been tested in people with AD [24, 25]. The estimated variability of 2% was taken from data on a memory-binding task for older individuals (aged 60–83) [26]. The standard deviation of the difference between the treatment and placebo was then calculated assuming equal variability in the two groups. This yielded an estimate of 3%. Using the two-sided test for paired means in PASS 11, the total sample required to detect a mean difference of 2.1% with a standard deviation of the difference of 3% and achieve 90% power at a 5% significance level in 24 patients.

Therefore, a sample size of 30 allows an attrition rate of 20% for the study still to be able to detect a meaningful difference in sensitive measures of cognitive function.

### Recruitment {15}

Participants will be recruited from Oxford University Hospitals NHS Foundation Trust (OUHFT) and Oxford Health NHS Foundation Trust (OHFT). The same method of recruitment will be applied at both sites.

Potentially eligible patients will be approached by a clinician who knows them and will be provided with an opportunity to hear more about the study. The initial approach will usually be made at the routine clinic visit for that patient. Eligible participants may initially be approached without their carer being present as all recruited patients must have capacity to consent to the ILIAD trial at screening.

Those interested will be provided with the PIS and either meet with a member of the research team on the same day (if the participant is able to do so) or given instructions on how to contact a member of the research team and arrange to meet at a mutually convenient time. The researcher will then go through the PIS and provide further information about the study. This meeting will occur in the out-patient clinic setting.

If the patient wishes to participate, they will be asked to provide verbal consent for the researcher to review their medical notes and screen against basic inclusion/exclusion criteria. If the patient appears eligible, they will be asked to give informed consent be enrolled into the trial. The patient will then undergo full screening including necessary blood tests, ECG recording and urinalysis. Should any patients, on full screening, be found to not meet all eligibility criteria, those patients will then be withdrawn.

At the same time as the patient is recruited, the patient’s carer will also be invited to participate in appropriate aspects of the study.

## Assignment of interventions: allocation

### Sequence generation {16a}

As ILiAD is a crossover trial, patients will be randomised 1:1 levetiracetam: placebo. All tablets of levetiracetam and placebo will appear identical. Restricted block randomisation will be performed by the Centre for Statistics in Medicine, University of Oxford, who will generate a series of randomisation codes. The investigators and patients will be blinded to treatment allocation.

### Concealment mechanism {16b}

The generated codes will be given to the Clinical Trial Pharmacist at St Mary’s Pharmaceutical Unit, Cardiff and Vale University Health Board, who will allocate each code to a pair of cartons of medication. Each of these two cartons will be labelled with the same randomisation code. One of the two cartons will be labelled Arm 1 and will contain seven packs of medication with each pack containing 40 tablets of levetiracetam/placebo. The other of the two cartons will be labelled Arm 2 and will contain seven packs of medication with each pack containing 40 tablets of levetiracetam/placebo. Within a given pair of cartons, if the carton labelled Arm 1 contains levetiracetam then the carton labelled Arm 2 will contain placebo and vice versa. This is illustrated in Fig. 4.

**Fig. 4 Fig4:**
[figure not shown]
Administration of IMP during the ILiAD trial. Randomised participants will attend site pharmacies to collect IMP as outlined. Each participant has a designated carton held at the trial pharmacies. IMP is randomly allocated as placebo or levetiracetam to arm1 and to arm 2. Participants then collect IMP from carton 1 and then carton 2 and titrate medication/placebo as per the administration schedules

### Implementation {16c}

The allocation system will be generated by the Centre for Statistics in Medicine, University of Oxford. The research team will enrol participants and recruited participants will be given a sequential identification number. Randomisation will occur after the baseline visit. The PI enrolling the patient will complete the ILiAD randomisation form. The site Pharmacy will dispense sequentially according to the Participant Trial ID Number.

## Assignment of interventions: blinding

### Who will be blinded? {17a}

Trial participants, care providers, principal investigators and all attending staff will be blinded to treatment allocation as none will know the code underpinning the treatment allocation. Investigators, patients and carers will remain blinded to the treatment allocation throughout the trial.

### Procedure for unblinding if needed {17b}

Unblinding should not normally be necessary as serious side effects will be dealt with on the assumption that the patient is on active treatment. Study medication should be omitted rather than unblinded. Request for unblinding should be directed to the Study Office during office hours. Each recruiting site will hold trial information for that site.

Given that levetiracetam is a well-established anti-seizure medication with a known side effect profile and is therefore considered a relatively low-risk IMP, out of hours code breaking is not thought to be required. However, to mitigate against any possible risk to participants, the main site, at the John Radcliffe Hospital, will have the CI’s mobile telephone number held at their Switchboard to enable prompt discussion about potential unblinding.

If a patient wishes to be unblinded for non-clinical reasons, the PI for that patient will submit a written request to the CI who will evaluate each participant wishing to be unblinded on a case by case basis.

Unblinding of a single patient will not lead to unblinding for the whole trial.

### Data collection and management

#### Plans for assessment and collection of outcomes {18a}

All trial staff will receive training in how to conduct the scales and assessments at a site initiation visit. The questionnaires to be administered in ILiAD (Addenbrooke’s Cognitive Estimate [27]; Bristol Activity of Daily Living Scale [28]; Dementia Severity Rating Scale [29]; Neuropsychiatric Inventory [30]; EQ5D [31]; Quality of life scale in AD [32]) are already used widely in clinical practice, and the computer-based task has been validated as a measure of hippocampal function [24–26].

Assessments will be completed according to the visit schedule.

#### Plans to promote participant retention and complete follow-up {18b}

The ILiAD study involves close co-operation between the participant and the research team. Potential participants and their carers will be fully informed of the visit schedule which we hope will ensure good retention of those recruited.

All randomised participants will be included in the analysis. Patients who withdraw from the study at any stage will be asked for permission for their data accumulated to the point of withdrawal to be included. Data from patients who have been unblinded will be included to the point of unblinding.

## Data collection and management {19}

Source documents include, but are not limited to, hospital records (from which medical history and previous and concurrent medication may be summarised into the CRF), clinical and office charts, laboratory and pharmacy records, diaries, microfiches, radiographs and correspondence. CRF entries will be considered source data if the CRF is the site of the original recording (e.g. there is no other written or electronic record of data). All documents will be stored safely in confidential conditions. On all trial-specific documents, other than the signed consent, the participant will be referred to by the trial participant number/code, not by name.

Each participant will have a designated trial folder. Carers will be allocated the same identification number as the participant followed by the word ‘CARER’. Data for cognitive, neuropsychiatric and psychosocial measures will be entered onto paper CRFs. These paper CRFs will be stored in the individual participant’s folder. Blood test results (with normal reference ranges) performed at screening will be printed onto a single sheet and stored in the participant’s folder. A redacted ECG performed within 3 months of enrolment will also be placed on file.

All documents will be stored securely and information from paper CRFs will be entered into the online RedCap electronic CRF system which is accessed securely through the University of Oxford webserver. Data entry into RedCap will be additionally supervised by the Trial Manager to ensure that there are no transcription errors. The participants will be identified only by a participant ID number on the paper CRF and any electronic database. Participants’ identification numbers and personal identification details will be stored separately in encrypted files on a password protected Oxford University server.

